### Recruitment procedures

Recruitment will take place in two steps: firstly, patients who were previously confirmed by neurologists for multiple sclerosis are referred to the neuro-physiotherapy clinic, Faculty of Rehabilitation Sciences, Iran University of Medical Sciences. Secondly, the assessor, who is a researcher, will conduct another screening for inclusion and exclusion criteria, will evaluate outcome measures, and make the final decision regarding the eligibility of the patients the same day; patients are referred to the clinic. If eligible, the patient will be provided with oral and written information about the study. Background information including name, contact number, height and weight, medical history, and medications used will be obtained from participants. Having signed a consent form by the treatment provider, patients will be randomized to one of the two treatment groups. and the assessment will be performed the same day of screening, in the physiotherapy evaluation laboratory in the School of Rehabilitation Sciences at the Iran University of Medical Sciences, Tehran.

One or two days later treatment sessions will be started in participants’ houses for 5 weeks (three times a week) by a treatment practitioner who is a physiotherapist with five years of experience in the field of neuro-physiotherapy. Because of the COVID-19 pandemic, all treatment sessions will be held in patient’s houses and the patients will come to physiotherapy evaluation laboratory for three times of assessment (baseline, one or two days after 15th session and 17 weeks after randomization day). All treatment sessions are free for all participants and the cost of any travel to the evaluation laboratory for assessment will be borne by the research team.

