### Interventions

At first, necessary explanations about the importance of exercise therapy in PWMS will be given to the participants. In both groups, exercise sessions will be delivered three times a week, over a course of 5 weeks, and the duration of each session will be 60 to 75 min. All 15 sessions will be supervised by the treatment practitioner at the participant’s houses individually due to COVID-19. In addition, the participants or their companions are required to make the home environment as safe as possible to minimize the likelihood of falling.

In two pamphlets, both groups will be given the exercises (DNS and CS) with the description required to do their exercises on days when the treatment practitioner is not present. In order to remind exercises to the participants, a reminder will be set on their cellphones. In addition, the participants will be instructed not to do any other exercises, nor receive other types of physiotherapy treatment during 5 weeks’ treatment sessions. If female participants get pregnant during the treatment plan or any fracture accrued during treatment sessions, they will be excluded.

Four barriers to exercise in PWMS are anticipated. The first is fatigue. Rest intervals are taken between specified exercises depending on one’s condition. Participants will be highly recommended to stop any exercise movement when they feel a lack of energy and any fatigue signs which are important in PWMS will be discontinued treatment sessions. The second is menstruation in women. The treatment session will be canceled on the first day of menstruation. The third is the time of the treatment session. The exercises will be performed in the morning or evening based on the participant’s comfort and level of energy. The fourth is medication. Treatment sessions will take place 48 h after the participant’s multiple sclerosis-related medications.

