### Outcome measures

All primary and secondary outcome measures will be measured by the blind assessor, who is a physiotherapy PhD student and completed a training course of biomechanical assessment tools, at baseline (a day before the first treatment session), the day after the final treatment session (15th session), and at a follow-up measurement after 17 weeks s. A home-based exercise program will be recommended for 17 weeks s’ follow-up based on their exercise group.

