### Data analysis

SPSS version 22 will be used for data analysis. We will perform an intention-to-treat analysis for dropout participants during treatment sessions and in follow-up assessment sessions. Conditional mean imputation was performed. Mean (standard deviation) or median (first quartile and third quartile) will be used to describe the quantitative variables according to the distribution of variables, and for categorical variables, frequency (percentages) will be used. Graphical methods, numerical indices, and Shapiro-Wilk’s tests will be used to check the normality of different measures.

To compare quantitative demographic variables between the two groups, an independent *t*-test or nonparametric test, Mann Whitney *U*-test will be used. Chi-squared or Fisher’s tests will be used to compare the categorical demographic variables between the two groups.

A separate regression analysis will be done at each follow-up point (i.e. the day after the completion of the 15th session (T2), and after 17 weeks follow-up (T3) each one including group and baseline (T1) as a covariate. The T2 and T3 follow-up point will be considered primary and secondary, respectively. A non-parametric analysis would be a Mann-Whitney *U*-test of the differences (follow-up minus baseline). A 2-tailed *P* < 0.05 will be considered significant.

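### The primary time point T2 is defined only by the 15th session, so a patient who stops sessions early has no defined T2 visit and, read literally, is imputed rather than measured

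*Protocol article*

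**What the plan says.** The Protocol article gives T2 in five places, each time by reference to session 15:

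- Data analysis: "the day after the completion of the 15th session (T2", followed by "The T2 and T3 follow-up point will be considered primary and secondary, respectively".
- Outcome measures: "the day after the final treatment session (15th session".
- Recruitment procedures: "one or two days after 15th session and 17 weeks after randomization day". This allows T2 one day more than the other sections and dates T3 from randomisation.
- The Methods paragraph of the Abstract and Sample size calculation also use the day after session 15. The latter makes that comparison the main goal on which the trial is sized.

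On patients who leave, Data analysis says "We will perform an intention-to-treat analysis for dropout participants during treatment sessions and in follow-up assessment sessions". The next sentence names conditional mean imputation, and no other handling is stated.

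On lost sessions, Interventions says "The treatment session will be canceled on the first day of menstruation". On fatigue it says "any fatigue signs which are important in PWMS will be discontinued treatment sessions". It also ties sessions to the timing of medication. The course is 15 sessions, three a week for 5 weeks, and no readable section says what happens to a cancelled session.

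**The concern.** An intention-to-treat comparison needs the outcome of every randomised patient, including those who stopped the exercises. When the visit is triggered by finishing the course, stopping treatment and losing the primary outcome become the same event. A patient who stops at session 8 could come to the laboratory in week 5, with her travel paid, but nothing in the text sends her there.

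Changing the imputation method later does not repair this, because a Berg score that was never collected cannot be recovered. What is at stake is whether the T2 result describes all randomised patients or, in effect, those who completed all 15 sessions.

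A second, smaller concern is timing. If cancelled sessions are added at the end of the course, T2 comes later for those patients than for others.

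**Working it through.** **1. The plan's own sample size.** Inputs from Sample size calculation and Data analysis: d = 0.8, two-sided 5%, power 80%, 1:1 allocation. A two-sample t-test needs 25.52, so 26 per group, which matches the plan. With 20% added, 26 × 1.2 = 31.2, so 32, which also matches. (Dividing by 0.8 gives 32.5, so 33; the difference does not affect this point.) Power at d = 0.8 is 80.7% with 26 per group and 88.3% with 32.

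**2. How many primary values could be imputed.** 20% of 32 is 6.4, so about 6 per arm if the whole dropout allowance were used. Some of these patients would be truly lost and would stay missing under any visit rule. The document does not split the allowance into patients who stop exercising and patients who cannot be reached.

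**3. When imputation misstates the difference.** Let p1 and p0 be the proportions stopping in the two arms, and s1 and s0 the amounts (in SD) by which stoppers fall short of completers in the same arm. Imputation from completers, given group and baseline, returns the completers' difference. The difference in all randomised patients is lower by p1·s1 − p0·s0. All values below are assumptions:

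| Stopping | Shortfall | p1·s1 − p0·s0 |
|---|---|---|
| 20% and 20% | 0.8 SD in both arms | 0.16 − 0.16 = 0 |
| 25% and 10% | 0.8 SD in both arms | 0.20 − 0.08 = 0.12 SD |
| 9 and 3 of 32 | 0.8 SD in both arms | 0.8 × 6/32 = 0.15 SD |
| 20% and 20% | stoppers keep none of the between-arm benefit, so s1 − s0 = 0.8 SD | 0.20 × 0.8 = 0.16 SD |

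The last row turns a completers' effect of 0.80 into 0.80 × (1 − 0.20) = 0.64 in all randomised patients. A simulation of the third row (10,000 runs, 32 per arm, assumed baseline correlation 0.6) gave 0.65 SD when everyone was measured and 0.80 SD when stoppers were imputed. If the arm with more stopping were reversed, the sign would reverse.

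**4. Precision.** In the same simulation with no true difference and 6 of 32 imputed per arm, treating imputed values as observed raised the two-sided type I error from about 5% to about 11%, even with balanced stopping. That is a fault of single imputation and could be cured by another method. It matters here because the visit rule adds to the number imputed.

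**5. Drift of T2.** 15 sessions at 3 a week fill 5 weeks. A cancelled session has three possible fates:

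- Moved within the same week: T2 does not change.
- Added at the end at 3 a week: T2 moves by 1/3 week per session, so 0.33 week for one and 1 week for three.
- Not made up: session 15 is never reached and T2 is undefined.

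The document does not say which applies. With an assumed 28-day cycle, at most two first days fall within 35 days, so menstruation alone could move T2 by at most 2/3 week.

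**6. The T3 anchor.** Recruitment procedures dates T3 17 weeks from randomisation. The Discussion places the 17-week follow-up after the exercise sessions. On the first reading the T2–T3 gap is about 17 − 5 = 12 weeks and shrinks if T2 is late. On the second it is 17 weeks and does not shrink.

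**The case against.** The strongest reply is that non-assessment of early stoppers is an inference. No sentence says that they are not seen. Recruitment procedures has patients attending three assessments without making this depend on attendance at sessions. Dropout could mean patients lost to assessment rather than patients who stop exercising. The course is described as 5 weeks, so T2 has a nominal week, and Table 1, which holds the schedule, is not shown. An article may leave visit windows and follow-up of those who discontinue to the full protocol. Assessing at the end of a fixed course is also a legitimate choice, because it aligns the arms on sessions received.

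Much of this stands. A reader might infer that the protocol excludes early stoppers from T2, but the text only leaves them without a defined visit. A reader might also infer that T2 slides for anyone with a cancelled session. It need not, since three individual home sessions a week leave other days free. The fatigue wording can be read as ending that day's session rather than leaving treatment, and nothing mentions stopping for poor response. A late T2 shortens the gap to T3 only on one of two conflicting statements of T3.

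What does not stand is that this is mere omitted detail. The article states the visit rule five times, always by session 15. It then names dropout during treatment sessions as a category of its own, separate from dropout at follow-up assessments, with imputation as the only handling. An analysis plan cannot supply data that the visit rule leaves uncollected.

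**Conclusion.** The point holds in a limited form. As worded, T2 is undefined for a patient who does not reach session 15, and the stated handling is to impute her primary outcome. This weakens the claimed intention-to-treat comparison at the primary time point. It rests on a literal reading of the text; the hidden table could give T2 as a week, in which case the text should be aligned with it.

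The size is not known. A reader might infer that the primary comparison is necessarily biased. The document does not support that: it gives no stopping rates or outcomes by arm, and balanced stopping with equal shortfalls gives no bias in the difference. The 0.12 to 0.16 SD in the unbalanced examples rests wholly on assumed inputs. Drift of T2 is possible but not inevitable. The planned 26 and 32 per group are unaffected as calculations at d = 0.8.

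**What to change.** In the Abstract, Recruitment procedures, Sample size calculation, Outcome measures and Data analysis, define T2 as one calendar visit at the nominal end of the 5-week course, with a stated window, for every randomised patient whatever number of sessions was completed. All five places must change together, or a new contradiction arises. In addition:

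- State that stopping sessions is not withdrawal from assessment, and that such patients are invited to T2 and T3.
- Record the number of sessions completed.
- Impute only when the visit itself is missed.
- Reconcile the day after session 15 with one or two days after it.
- Reconcile the two T3 anchors (Recruitment procedures and Discussion).
- For patients already past T2, report how many had no visit because session 15 was not reached.

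The cost is mainly wording, since the visit, the laboratory and travel payment already exist. There are two downsides. Some patients will be assessed before sessions that are made up later. Including non-completers may also bring the effect below the planned 0.8: at an assumed d = 0.64, a two-sided t-test with 32 per arm fully observed has about 71% power, against 88.3% at d = 0.8. This should be acknowledged when the visit is redefined.

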### Sample size calculation

This study, for the first time, compares DNS exercises with CS exercises in PWMS. Due to the lack of previous studies and considering the main goal of study as comparing two groups the day after the completion of the 15th sessions, the Cohen standardized effect size for comparing means of two independent groups was used in this study to calculate the sample size. Considering the probability of the first type error of 5%, the power of 80%, the standard Cohen’s effect size of 0.8, and using G-Power software the sample size was calculated as 26 subjects in each group which increased to 32 subjects to assume the 20% of dropout rate. Another power calculation will be performed at the end of the trial to assure the sufficiency of the sample size.

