##### Berg Balance Scale

Berg Balance Scale is a validated tool to measure a patient’s static and dynamic balance. It consists of 14 items (scores from zero to 56) and is a valid and reliable test for PWMS [35]. Berg Balance Scale measures balance in sitting, standing, and most daily activities (such as sitting up, moving from chair to chair, standing with eyes closed).

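### The non-parametric alternative to the baseline-adjusted regression is a Mann-Whitney test of change scores: it drops the baseline covariate, has no stated trigger, and costs power in every scenario examined

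*Protocol article*

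**What the plan says.** The Data analysis section contains three relevant statements.

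- **Main analysis.** A separate regression at T2 and at T3, each with group and the T1 value as covariates. T2 is primary and T3 secondary.
- **Normality check.** In an earlier paragraph, after the choice of descriptive statistics, graphs, numerical indices and Shapiro-Wilk "tests will be used to check the normality of different measures".
- **Non-parametric option.** A Mann-Whitney test "of the differences (follow-up minus baseline". No condition for using it is given.

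The primary outcome is the Berg Balance Scale: "It consists of 14 items (scores from zero to 56".

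The Sample size calculation section uses "the probability of the first type error of 5" percent, "the power of 80" percent and an effect size of 0.8. It describes an unadjusted comparison: the "effect size for comparing means of two independent groups was used in this study". This gives 26 per group, raised to 32 for dropout. The test is two-sided: "A 2-tailed *P* < 0.05 will be considered significant".

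**The concern.** Three features of the named alternative are weak.

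1. **It drops the covariate.** The main model gains precision by conditioning on baseline. Subtracting baseline and ranking the result gives up part of that gain. It also yields no baseline-adjusted difference in Berg points, so it answers a somewhat different question.
2. **The check is aimed at the wrong object.** The regression needs reasonably behaved residuals, not normal raw scores. On a scale with a ceiling the two can disagree sharply.
3. **The trigger is open.** If the Mann-Whitney test is a fallback, the choice between two analyses of the primary question is left until the outcome data are in hand.

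A further consequence concerns a secondary outcome. Applied to Modified Ashworth grades (0 to 4), the test of differences subtracts ordinal grades as though the steps were equal.

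At stake is efficiency. Under some plausible conditions the trial could have materially less chance of detecting the effect it was sized for.

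**Working it through.** **Inputs from the article.** Two-sided alpha 0.05; d = 0.8; 26 evaluable per arm (32 randomized); Berg capped at 56.

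**Inputs not in the article (assumed, shown as ranges).** The baseline-to-T2 correlation r, the Berg mean and SD, and any rise common to both arms.

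**Step 1: the plan's own figure.** For two independent means, the noncentrality is d × √(n/2). With n = 26 this is 0.8 × √13 = 2.88, which on 50 degrees of freedom gives power 80.7%. With n = 25 power is 79.1%. The stated 26 is reproduced.

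**Step 2: efficiency under normality.** Let the SD be 1 at each time point.

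- Regression on baseline: residual variance 1 − r², so effective size d/√(1 − r²).
- Change score: variance 2(1 − r), so effective size d/√(2(1 − r)).
- Variance ratio, change to regression: 2(1 − r)/(1 − r²) = 2/(1 + r). This is 1.54 at r = 0.3, 1.33 at 0.5 and 1.18 at 0.7.
- Mann-Whitney on normal data has asymptotic relative efficiency 0.955, a further loss of about 4.5%. Its effective size is the change-score size × √0.955.

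**Step 3: power with 26 per arm, d = 0.8, no ceiling (noncentral t).**

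| r | Size, regression | Size, Mann-Whitney on change | Power, regression | Power, Mann-Whitney on change |
|---|---|---|---|---|
| 0.2 | 0.816 | 0.618 | 82% | 59% |
| 0.3 | 0.839 | 0.661 | 84% | 65% |
| 0.4 | 0.873 | 0.714 | 87% | 71% |
| 0.5 | 0.924 | 0.782 | 90% | 79% |
| 0.6 | 1.000 | 0.874 | 94% | 87% |
| 0.7 | 1.120 | 1.009 | 98% | 95% |
| 0.8 | 1.333 | 1.236 | 99.7% | 99% |

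Simulation (2,000 trials per row) agreed to within about 2 to 3 points. The Mann-Whitney option reaches 80% at r of about 0.51 with 26 per arm, and at about 0.40 if all 32 per arm are evaluable.

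**Step 4: the ceiling.** Simulated trials (1,500 per scenario, 26 per arm) had scores rounded and capped at 56, a 2-point rise in both arms and d = 0.8 before capping. The SD is 6; all Berg levels are assumed.

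| Baseline mean | Share at 56 at T2 | Shapiro-Wilk rejects raw T2 scores (either arm) | Shapiro-Wilk rejects residuals |
|---|---|---|---|
| 40 | 4% | about 15% | about 5% |
| 45 | 17% | about 87% | 7–23% |
| 48 | 32% | nearly 100% | 11–62% |

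| Baseline mean | Power, regression (r = 0.3, 0.5, 0.7, 0.8) | Power, Mann-Whitney on change (same r) |
|---|---|---|
| 45 | 82, 89, 96, 99% | 57, 71, 87, 96% |
| 48 | 78, 84, 94, 99% | 49, 58, 76, 89% |

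The Mann-Whitney option was the weaker test in every scenario. At an assumed mean of 45, testing raw scores would reject normality in most trials, while testing residuals would do so in a minority.

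**The case against.** The strongest reply has five parts.

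- **No switch is stated.** The regression is described without condition, and the normality sentence sits with the descriptive statistics. The Mann-Whitney sentence could describe a sensitivity analysis or a method for ordinal secondary outcomes. This stands: a reader might infer an explicit rule replacing the regression when normality is rejected, but the article contains none. A fallback is a reasonable reading, not the only one.
- **Frequent use is not shown.** A reader might infer from the cap of 56 that the fallback is likely to be triggered. The article gives no expected Berg mean, SD or share at the cap, and it requires a recent fall for entry, so crowding near 56 cannot be presumed. The simulated rejection rate runs from about 5% to nearly 100%, depending on the assumed level and on what is tested. This stands.
- **A drop well below 80% is conditional.** The design's 80% is for an unadjusted comparison. At r = 0.5 the change score has the variance of the raw score, so the fallback's 79% is close to the design's 80.7%; much of the gap to 90% is lost gain rather than a shortfall against plan. At r = 0.6 or more with little ceiling, the fallback keeps 87% or more. This stands.
- **Part of the capped loss belongs to the scale.** At mean 48 and r = 0.3 the regression itself falls to 78%. Only the difference between the two tests is due to the choice of test.
- **No false-positive inflation is shown.** Both tests are named in advance, a normality check does not select on the treatment effect, and the analyst is blind to allocation. This stands; the point is about efficiency, not validity.

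A fuller analysis plan, not shown, might define the trigger. That would not change the named method, which omits the covariate the main model uses.

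**Conclusion.** The concern holds in a limited form. The article names, as its non-parametric alternative, a test that ignores baseline, states no trigger for it, and describes the normality check as being on the measures. If used as a fallback, it costs power at every correlation below 1 under normality: about 19, 11 and 3 percentage points at r = 0.3, 0.5 and 0.7 with 26 per arm and d = 0.8. It takes power below the planned 80% only if r is under about 0.5 (about 0.4 if all 32 per arm are evaluable) or if many patients are near the cap.

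The correlation, the Berg distribution and the common rise are assumptions. The documents therefore support neither a claim that the trial will be underpowered nor one that the fallback will usually be used. The matter is still worth correcting, because a better method costs nothing and the plan already contains it.

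**What to change.** 1. State that the primary analysis of the Berg Balance Scale at T2 is the regression on group and baseline Berg score, whatever the normality tests show.
2. Make any distributional check on the regression residuals. If they look poor, keep the same model and use robust standard errors or a permutation p-value.
3. Where a rank-type analysis is wanted, including for Modified Ashworth grades, use one that adjusts for baseline, such as ordinal regression of the follow-up score on group and baseline, or rank ANCOVA.
4. Keep the Mann-Whitney test of differences only as a labelled sensitivity analysis, or remove it.

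The cost is a few sentences of analysis wording. No patients, visits or data items change.
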